### Outcomes

Selection of outcome measures was based on a previously developed core outcome set designed for hospital-based deprescribing interventions.^17^ The primary outcome measure was selected as hospital readmission within 90 days as this was considered to be sufficiently sensitive and proximal to the intervention.

Outcome data are summarised in table 1. Costs and resource use, as well as economic outcomes, will be captured via expert opinion and review of study records where relevant.

**Table 1 T1:** Outcome data

Routinely collected data (without consent)	When	How
Mortality for any reason	90 data post-discharge	Hospital records and NHS England* Office of National Statistics Mortality records
Number of hospital stays†	90 data post-discharge	Hospital records and NHS England* Hospital Episode Statistics Admitted patient care
Number of planned and unplanned admissions and readmissions for treatment or monitoring of health†		

Intensive data collection (with consent)¶	When	How
Satisfaction with deprescribing process‡	2 weeks post-discharge	Postal questionnaire
Adverse drug events§	90 days post-discharge	Telephone questionnaire
Health-related quality of life (EQ-5D-5L††)^23^	Pre-discharge 90 days post-discharge	Face to face on ward Telephone questionnaire
Primary care consultations†	90 days post-discharge	Telephone questionnaire
Community pharmacy dispensed medicines†	90 days post-discharge	NHS England*
Number of ‘Regularly’ prescribed medicines	On admission and discharge	Routine hospital records^**^
Number of ‘As required’ prescribed medicines		
Number of medicines prescribed on admission which are stopped during admission while on study ward		
Number of medicines prescribed on admission with dosage reduced during admission while on study ward		
Number of stopped medicines prescribed on admission which are stopped during admission while on study ward and then restarted		

* National agency responsible for collation and provision of healthcare data.

† Captured for additional health economic analysis purposes.

‡ Questionnaire with 12 items based on previously published survey tool.^25^

§ Questionnaire with 17 items inviting respondents to indicate whether or not they have experienced any of the medication-related adverse events listed. The list is derived from an observational study of medication-related adverse events.^26^

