### Sample size

The underpinning feasibility study showed that recruitment to an original planned cluster randomised trial would require recruitment of over 40 hospitals and was unlikely to be achieved. Consequently, the design was changed to a stepped wedge due to the increased power provided by this design.

With a baseline step with all hospitals receiving the control followed by four separate steps, each randomising five hospitals to switch from control to intervention (20 hospitals in total) will have 89.5% power to detect a difference of 16.7% to 13.7% of 90-day re-admission rates assuming a 5% level of significance and an intra-class correlation coefficient (ICC) of 0.05 and 200 participants per hospital per step. The total sample size will be 20 000 participants. The anticipated 3% difference is similar, but slightly smaller, to the difference reported in the MedSafer study.^19^

From our feasibility study findings, we estimate that 10% of patients on study wards or consultees will provide written (or, if required, virtual) informed consent for additional patient-reported outcome data. For the enhanced data collection period, where medication changes are recorded in hospital, then if the sites collect data on 60 participants in each of the enhanced data collection periods, the study will have 99.99% power to detect an average change of 0.5 medications between the control and intervention phase, assuming a SD of 1.5 medications, a 5% level of significance and an ICC of 0.05.

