### Recruitment

All patients receiving treatment under the care of participating geriatricians on the study wards within the study window (1 February 2024 to 31 July 2025) will be eligible for inclusion.

With national CAG^20^ permission, all patients admitted to wards under the care of participating consultant geriatricians will be enrolled for routine data collection purposes, enabling collation of the primary outcome measure for all patients. Consequently, we will not be required to enact any strategies for achieving adequate participant enrolment.

During enhanced data collection periods, 1 month during the control period and 1 month during the intervention period, patients admitted to wards under the care of participating consultant geriatricians will be approached to be consented for enhanced data collection, that is, non-routinely collected data needed for secondary outcome measures and process evaluation purposes.

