### Assignment of interventions: allocation

#### Sequence generation

Sites will be randomised to the four ‘groups’, the ‘groups’ being the step at which they started the intervention. Group 1 will start the intervention on the first step, etc. A fifth group, Group 5, is the reserve list. To ensure no two sites from the same region are randomised to the same group and thereby overwhelm the local RDN team, randomisation will be stratified by region. A block size of 4 will be used so that randomisation could occur once four sites are recruited and concealment maintained.

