### Statistical methods for primary and secondary outcomes

#### Characterising and comparing sites

Participating hospitals and geriatricians and pharmacists will be characterised using descriptive statistics from the hospital site profile questionnaire and practitioner participant demographic questionnaire. Data will be visually compared with data captured from NHS Improvement’s hospital provider level benchmarking tool ‘model hospital’^22^ regarding the number and cost of staff on medicine for older people’s medicine wards. Demographic characteristics of patients between all study wards of the participating hospitals will be visually compared to explore whether they are comparable. For the sample of patients in the study cohort from whom consent is obtained either from the patient or consultee for additional non-routine data to be collected, the demographic characteristics of this group will be visually compared with the wider study cohort. This will establish whether the sub-set of patients for whom additional data are collected is a good representation of the patient cohort in the study.

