#### Main effectiveness analysis

The primary analysis will be using intention-to-treat with a pre-specified statistical analysis plan (SAP) agreed prior to analysis. Analysis will be at the patient level and include data from all patients.

Unplanned readmission at 90 days, primary outcome measure, will be compared between the treatment and control groups using a logistic mixed regression model with hospital included as a random effect, and fixed factors will include randomisation arm and time period. If a significant number have more than one readmission, then a Poisson or Negative binomial model will be used as a secondary analysis. The assumptions of the models will be checked and, if appropriate, a Generalised Estimating Equation approach will be used if the random effect is not normally distributed, or a non-parametric bootstrap approach will be used to account for missing data.

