#### Additional analyses

A sensitivity analysis will adjust for relevant baseline characteristics, that is, age and the number of pre-admission medicines.

The number of medications stopped during the enhanced data collection period will be compared between the control and intervention using a linear mixed model including hospital as a random effect, and fixed factors will include randomisation arm and time period.

The proportion of patients per arm where a pre-admission medicine is proactively deprescribed will be compared using logistic regression, the same model as above.

The QoL measures will be compared between the control and intervention using a linear mixed model including hospital as a random effect, and fixed factors will include randomisation arm and time period.

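### The primary model omits age and the randomisation stratum, and the only planned age-adjusted analysis may not cover all primary-analysis patients

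*Protocol article*

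**What the plan says.** Five places in the protocol article bear on this.

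- **Main effectiveness analysis.** The primary comparison is a logistic mixed model with "hospital included as a random effect, and fixed factors will include randomisation arm and time period". It is a patient-level, intention-to-treat analysis of all patients.
- **Sequence generation.** Hospitals are allocated to steps and "randomisation will be stratified by region". The reason given is operational: "To ensure no two sites from the same region are randomised to the same group", so that no local research delivery team is overloaded.
- **Additional analyses.** "A sensitivity analysis will adjust for relevant baseline characteristics, that is, age and the number of pre-admission medicines". No other analysis of the primary outcome is said to adjust for age.
- **Outcomes, Table 1.** Medicine counts, for example "Number of ‘Regularly’ prescribed medicines" on admission and discharge, stand in the block for intensive data collection with consent, not in the block of routine data held without consent.
- **Characterising and comparing sites.** "Demographic characteristics of patients between all study wards of the participating hospitals will be visually compared", and the consented subset is compared with the wider cohort. This implies, without saying so outright, that age is held for everyone.

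**The concern.** In a stepped wedge with a new group of patients in each period, different people make up a hospital's control and active phases. A random hospital effect removes stable differences between hospitals, and a period effect removes changes common to all hospitals. Neither removes a change in one hospital's patient mix that coincides with its own switch. Age is the obvious covariate to guard against this, and it appears to be available for all patients. The plan keeps it out of the headline model.

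The planned safeguard has a gap. Because age is paired with the medicine count, the adjusted analysis can only include patients who have that count. If the count exists only for the enhanced months, no age-adjusted result is planned for most of the primary population.

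Region is a separate and smaller matter. It is a design factor, and the usual practice is to carry design factors into the model. It does nothing about case mix that changes within a hospital over time.

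**Working it through.** **Inputs from the Sample size section.** 20 hospitals; a control baseline and four steps of five hospitals, so 5 periods; 200 patients per hospital per step; ICC 0.05; 5% level (taken as two-sided); and "89.5% power to detect a difference of 16.7% to 13.7% of 90-day re-admission rates".

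**1. Reproduce the stated power.** Use the Hussey–Hughes generalised least squares variance with a random hospital intercept, fixed periods and a treatment term.
- Total variance: 0.167 × 0.833 = 0.1391.
- Split at ICC 0.05: 95% within hospitals, 5% between.
- SE of the risk difference: 0.00933.
- Power: Φ(0.03 / 0.00933 − 1.96) = 89.5%, which agrees with the article.

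**2. Add age.** Multiply the within-hospital variance by (1 − R²). The documents give no R², so these values are assumed.

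| Share of within-hospital variance explained by age | Power | Gain (points) |
|---|---|---|
| 0.5% | 89.7% | 0.1 |
| 1% | 89.8% | 0.3 |
| 2% | 90.1% | 0.6 |

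**3. Add region.** Multiply the between-hospital variance by (1 − share) and include fixed region effects. The number of regions is not stated. Five regions with one hospital in each step are assumed.

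| Share of between-hospital variance explained by region | Power | Gain (points) |
|---|---|---|
| 30% | 89.7% | 0.1 |
| 50% | 89.9% | 0.3 |
| 80% | 90.8% | 1.2 |

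With nine unevenly spread regions and a 50% share, power is 89.8%. The gain is small because each hospital already serves largely as its own control. Age (1%) and region (50%) together give 90.2%.

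**4. Size the case-mix risk.** A one-year rise in mean age changes risk by about 0.167 × 0.833 × slope. For assumed log-odds slopes of 0.01, 0.02 and 0.03 per year this is 0.14, 0.28 and 0.42 percentage points. How far that reaches the trial estimate depends on each hospital's weight:
- *One hospital shifts.* In the design of step 1, a hospital's weight for a shift at its own switch is 0.042, 0.060, 0.059 or 0.039, by randomised group. The estimate moves by between 0.14 × 0.039 = 0.005 and 0.42 × 0.060 = 0.025 points, under 1% of the 3-point target.
- *All hospitals shift independently, SD one year.* The root of the summed squared weights is 0.228, so the typical movement is 0.14 × 0.228 = 0.03 to 0.42 × 0.228 = 0.10 points. This is noise, against an SE of 0.93 points.
- *All 20 hospitals shift one year in the same direction, each at its own switch.* The weights sum to 1, so the estimate moves by the full 0.14 to 0.42 points, or 5 to 14% of the target.

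**5. Reach of the planned adjusted analysis.** The Sample size section uses 60 participants per site in each of two enhanced periods: 20 × 2 × 60 = 2,400. Against 20,000 patients this is 12%. If medicine counts exist only there, the age-adjusted analysis would leave out about 88% of the primary population.

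**The case against.** Several points on the other side stand in whole or in part.

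- **Selection is limited by design.** With permission to use routine data without consent, "all patients admitted to wards under the care of participating consultant geriatricians will be enrolled for routine data collection purposes", apart from national opt-outs. Lack of blinding therefore has no consent-based route into the primary population, and the intervention targets prescribing behaviour, not admissions. This stands. What remains is that participating geriatricians can withdraw and be replaced, so the mix of patients under them is not fixed.
- **A lightly adjusted primary model with an adjusted sensitivity analysis is a legitimate order.** This stands as a general principle. It is weakened here because the adjusted analysis also needs the medicine count and so may not reach all patients.
- **The list of fixed factors is not worded as exhaustive, and the statistical analysis plan takes priority.** This is true, and that plan is not at hand. However, the article states where age goes, so its placement is a choice already made and not a detail left open.
- **Table 1 gives routine hospital records as the source of the medicine counts.** They might be extractable more widely. For that reason the coverage gap is a possibility, not a certainty.

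Two stronger readings are tempting. A reader might infer that a hospital-specific age shift biases the result by 5 to 14% of the target effect. That size needs the same shift in every hospital at its own staggered switch, and the documents give neither a mechanism for this nor an age slope. A reader might also infer that leaving out region costs material precision or leaves case mix uncorrected. The hospital effect already absorbs most stable regional differences, and region has no bearing on change within a hospital.

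**Conclusion.** The point holds in a limited form. The stated primary model leaves out a covariate that the article calls relevant and appears to hold for everyone, and it leaves out the randomisation stratum. The one planned age-adjusted analysis is tied to a variable listed under enhanced data collection and may not cover the primary population.

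The consequences are small. Under the assumed variance shares, power rises by roughly half a point or less from age and by no more than about 1.2 points from region. The case-mix risk is real in principle but modest, and the documents give nothing to size it with. No bias has been shown, and the stated 89.5% power is not in question here. The improvement is worth making because it is cheap, and because it makes the headline result the better protected one.

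**What to change.** In the statistical analysis plan, and in the protocol text if it is amended:

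1. Include age as a continuous term in the primary model for all patients, and report the model without age as the sensitivity analysis.
2. Make adjustment for the number of pre-admission medicines a separate analysis, restricted to patients who have that count, and state how many they are expected to be.
3. Add region as a random effect, or as fixed effects if regions are few, to match the randomisation.

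The cost is wording only, before any data are analysed. There are two downsides. The odds ratio becomes conditional on age and region. Fixed region terms also use a few cluster-level degrees of freedom out of only 20 hospitals, which favours the random effect when there are many small regions.

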#### Handling missing data

Due to the use of routinely collected data, it is unlikely that there will be significant missing data for the main analysis. If appropriate, we will use imputation to account for missing data for other non-routine outcomes.

A full SAP will be written prior to the start of any data analysis. As the SAP will be more detailed, any discrepancies in the analysis between the SAP and the protocol, the SAP will take priority.

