If the intervention arm is both less expensive, for example, due to lower medication or readmission costs, and more effective than usual care in terms of the primary outcome of readmissions at 90 days, then it would be said to dominate usual care and would be the preferred option. If neither the intervention nor the usual care is clearly preferred, we will estimate incremental cost-effectiveness ratios in terms of cost per re-admission prevented.^12^ The associated level of uncertainty will be characterised by estimating cost-effectiveness acceptability curves. Sensitivity analysis will also be undertaken to assess the robustness of results to changes in key assumptions. In line with the outcome analysis, all analyses will be conducted on an intention-to-treat basis. Appropriate actions will be taken where there is missing data, for example, imputing data by means of multiple imputation. As part of the health economic analysis, a health economics analysis plan will be written, in consultation with the CI and trial statistician and shared with team members.

A health economic model will be constructed to explore the effects of long-term changes in prescribing costs and mortality. The exact form of this model will be established in consultation with other members of the research team, as a clinical input to this process would be vital. A priori, this would be expected to take the form of a Markov model estimating cost per QALY.

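### A non-parametric bootstrap is the only method named for missing primary-outcome data, and it cannot account for them; the likely effect is small

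*Protocol article*

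**What the plan says.** Under Main effectiveness analysis, the article promises that "Analysis will be at the patient level and include data from all patients". The primary model is a "logistic mixed regression model with hospital included as a random effect, and fixed factors will include randomisation arm and time period". The same paragraph then gives fallbacks to be used where appropriate after model checking: generalised estimating equations if the random effect is not normal, or "a non-parametric bootstrap approach will be used to account for missing data".

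Under Handling missing data, it says that "it is unlikely that there will be significant missing data for the main analysis", because the data are routinely collected, and then: "If appropriate, we will use imputation to account for missing data for other non-routine outcomes". Multiple imputation is named once, as an example, under Health economics: "Appropriate actions will be taken where there is missing data, for example, imputing data by means of multiple imputation". On precedence, "any discrepancies in the analysis between the SAP and the protocol, the SAP will take priority".

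Two groups of patients are absent by design. A footnote to Table 1 says that routine data were not collected for people who declined consent or assent in the enhanced data collection periods. Participant timeline excludes patients who had already opted out of research use of their NHS data.

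**The concern.** The article names a method and gives it a task that the method does not perform. A bootstrap estimates sampling variability. If records with an observed outcome are resampled, every replicate carries the same selection as the original complete cases, so the bootstrap distribution centres on the complete-case estimate. Adjustment for missing outcomes has to come from imputation, weighting or a model for the missingness, and the sentence mentions none of these. Imputation is directed elsewhere.

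At stake is a report which says that missing primary outcomes were accounted for when the estimate is simply the complete-case one. That matters only if outcomes are missing in a way related to readmission and different between control and intervention phases.

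**Working it through.** **1. The plan's own figure.** Inputs from Sample size: 20 hospitals, a baseline period plus four steps (T = 5), 200 patients per hospital per step, ICC 0.05, 5% significance (taken as two-sided), 16.7% against 13.7%. I used the Hussey-Hughes variance, with total variance at the control rate, 0.167 × 0.833 = 0.13911.

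- s² = 0.13911 × 0.95 / 200 = 0.00066078; t² = 0.13911 × 0.05 = 0.0069556.
- For this layout I = 20, U = 50, W = 750, V = 150.
- Var = I·s²(s² + T·t²) / [(IU − W)s² + (U² + ITU − TW − IV)t²] = 20 × 0.00066078 × 0.035439 / (250 × 0.00066078 + 750 × 0.0069556) = 0.00008702.
- SE = 0.933 points, and power = Φ(3.0/0.933 − 1.96) = 89.5%, as stated.
- 20 × 5 × 200 = 20 000 matches the stated total, so it includes no allowance for missing outcomes.

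**2. What missingness costs in precision alone.** If outcomes are missing completely at random, the same formula with 190 or 180 per hospital per step gives 88.0% power at 5% missing and 86.3% at 10%. Precision is not the issue.

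**3. What the bootstrap does.** Assumed set-up: no true effect; a binary risk factor in half the patients, with readmission 21.7% or 5.7% (mean 13.7%); 10% missing in high-risk intervention patients and 2% in all others. The expected complete-case rate under intervention is (0.45 × 21.7 + 0.49 × 5.7)/0.94 = 13.36%, against 13.7% under control, a spurious −0.34 points. One simulated data set of 200 000 patients gave:

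| Estimate | Difference (points) |
|---|---|
| Full data | +0.14 |
| Complete case | −0.27 |
| Bootstrap mean (300 draws) | −0.27 (SD 0.16) |
| Standardised on the risk factor | +0.08 |

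The bootstrap returns the complete-case value. A method that uses the covariate recovers most of the gap.

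**4. How large the bias could be.** The documents give no missingness rate, so every input here is assumed. If a fraction m is missing and the missing have RR times the risk of the observed, observed rate = true rate / [(1 − m) + m·RR].

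| Missing, control / intervention | RR | Observed rates | Difference seen (true 3.0) |
|---|---|---|---|
| 8% / 4% | 2 | 0.167/1.08 = 15.46%; 0.137/1.04 = 13.17% | 2.29 |
| 5% / 2% | 2 | 0.167/1.05 = 15.90%; 0.137/1.02 = 13.43% | 2.47 |
| 10% / 5% | 1.5 | 0.167/1.05 = 15.90%; 0.137/1.025 = 13.37% | 2.54 |

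The direction can reverse. With no true effect (16.7% in both phases), 5% missing under intervention only and 30% of those readmitted, the observed rate is (0.167 − 0.05 × 0.30)/0.95 = 16.0%, an apparent benefit of 0.70 points. If the missing have the same rate as the rest, the bias is zero.

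**5. When there is no bias.** The model already conditions on hospital, period and phase, so missingness that depends only on these does no harm. On the odds-ratio scale of the planned logistic model, missingness that depends on the outcome equally in both phases also cancels. With 5% missing, doubled if readmitted, each phase's odds are multiplied by 0.90/0.95, and the odds ratio stays at 0.792.

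**6. Would imputation repair it?** Not if missingness depends on readmission itself. With 5% (control) and 2.5% (intervention) missing, doubled if readmitted, the complete-case difference is 2.57 points. Imputing on a binary covariate with risk ratio 1.5 to 3 gives 2.57 to 2.59 or 2.60, depending on whether half or 30% of patients carry it. At 8% and 4% it is 2.27 before imputation and 2.27 to 2.32 after. Imputation helps in the setting of step 3, not in this one; hence the sensitivity analysis in the fix.

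**The case against.** The clause is a condensed, conditional fallback in a sentence about model assumptions. It may be a slip for a bootstrap meant to handle a badly behaved random effect, and it does not rule out imputation within each replicate. The SAP, which is not shown, takes priority. The article expects little missing data, and its two stated routes to absence leave no evident record from which to impute.

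Most of this stands as a limit on size. It does not rescue the sentence, which assigns the bootstrap to missing data and mentions no imputation step, while the imputation sentence points to other outcomes. Leaving detail to a SAP is normal; naming a method that cannot do the stated job is a different matter.

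A reader might infer that patients who fail to link to national records will bias the result, by 0.5 to 0.7 points. The documents do not support that. They do not mention failed linkage, they give no missingness rate, and nothing in them shows that absence differs by phase or is related to readmission. A patient not found in the national record might also be counted as not readmitted, which would be misclassification and not missingness.

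A reader might also infer that hospital records could simply fill any gaps. Table 1 lists hospital records beside NHS England data for hospital stays, but nothing shows that they capture unplanned readmissions to other hospitals. Using them for only some patients could introduce misclassification.

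**Conclusion.** The stated rule is wrong as written. A bootstrap of observed patients leaves the complete-case estimate where it was, and no other method is named for missing primary outcomes in the effectiveness analysis. This rests on reading the clause as plain resampling, which is all that it says.

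The likely consequence is small. Bias requires missingness that is related to readmission beyond hospital, period and phase, and that also differs by phase. The range of 2.3 to 2.5 points seen for a true 3.0 illustrates assumed rates and does not estimate what will happen. The correction is worth making because it is cheap and because it prevents a claim in the final report that the analysis could not support.

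**What to change.** - Delete the bootstrap as a way of accounting for missing data. If it is kept, resample whole hospitals and use it only for confidence intervals.
- If primary outcomes are missing for enrolled patients, report the complete-case mixed model beside multiple imputation that uses hospital, period, phase and collected patient variables such as age and 90-day death.
- Add a sensitivity analysis in which missingness depends on readmission and differs by phase, because ordinary imputation leaves that kind of bias almost untouched (step 6 of the working).
- Report by phase the number of patients whose routine data were not collected because they declined. Imputation cannot recover them.
- Do not substitute hospital-record readmission status for some patients unless it is shown to capture unplanned readmissions to other hospitals.

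The cost is a short correction to the text, carried into the SAP, and a small amount of extra analysis if outcomes prove to be missing. No new outcome data are needed.
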